### Participants

#### Recruitment

Five hundred and forty (540) participants are recruited over a period of 6 months through an invitation letter by one of the seven cooperating municipalities. Each municipality will select two groups for participation, who originate from one or more comparable residential areas or neighborhoods based on their socioeconomic status. Neighborhood selection is based on data of www.waarstaatjegemeente.nl, a website where municipalities can compare their own data with other municipalities on themes such as youth aid, finances and sustainability. These comparable neighborhoods are randomly assigned to either the experimental group or the waiting list control group [50]. Names and addresses of independently living men and women aged 65 years or older residing in these municipalities are drawn from the records of the residents’ registration office taking the General Data Protection Regulation of the European Union into account. The number of persons drawn from the records varied between 500 and 4000 per municipality.

#### Eligibility criteria

Participants must be 65 years or older, be fluent in Dutch and suffer from at least one chronic illness that affects mobility (e.g. musculoskeletal and back disorder, COPD, rheumatism, osteoporosis, chronic heart disease) or other physical conditions (e.g. visual or hearing impaired) that may affect mobility. Participants with self-reported cognitive problems or wheelchair users are excluded from the study. Participants must be able to walk at least 100 m, possibly with the help of a rollator or walking stick.

#### Procedure

Figure 1 provides an overview of the study procedure. Residents from both the selected experimental and the waiting list control neighborhoods receive an invitation letter and an informed consent from their municipality. The informed consent contains a list with the most common chronic conditions that affect mobility with which interested residents can check their eligibility. When interested residents suffer from at least one chronic condition, they can send their informed consent to the researchers. Subsequently, eligibility criteria are checked in the informed consent and by a phone call with the research assistant. With all eligible persons an appointment is set for the cognitive functioning test.

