## Methods

### Study design

The study is a parallel, two-group cluster-RCT with a waiting list control group and assessments at baseline, six and 12 months. Due to the nature of the study, it is not possible to blind the researchers. Participants do not know there are two groups being examined. Ethical approval for the study was obtained from the Research Ethics Committee (cETO) of the Open University and the trial is registered with the Dutch Trial Register, protocol number NL6005. This protocol is reported in accordance with SPIRIT guidelines. The study is funded by a grant from the Brain Foundation Netherlands. All participants provide written informed consent prior to commencing the study. Participants may withdraw from participation at any time without giving an explanation, no data will be collected anymore. There are no interventions or care prohibited during the trial.

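### Neighbourhoods are allocated before residents are invited, and no step keeps the arm from the staff who screen by phone and test at baseline

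*Protocol article*

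**What the plan says.** All of this is in the protocol article.

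- **Recruitment.** Each municipality selects two comparable groups, each from one or more neighbourhoods. "These comparable neighborhoods are randomly assigned to either the experimental group or the waiting list control group". The drawing of names from the residents' register is described after this.
- **Procedure.** "Residents from both the selected experimental and the waiting list control neighborhoods receive an invitation letter and an informed consent from their municipality". Interested residents check a list of conditions themselves and return the consent form. Then "eligibility criteria are checked in the informed consent and by a phone call with the research assistant". The accelerometer week, the home cognitive test and the baseline questionnaire come next, and the intervention starts only after these.
- **Eligibility criteria.** Participants need an illness or other condition that affects, or may affect, mobility, and must be able to walk 100 m. "Participants with self-reported cognitive problems or wheelchair users are excluded from the study".
- **Study design.** "Due to the nature of the study, it is not possible to blind the researchers". The same section states: "Participants do not know there are two groups being examined".

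The article does not describe concealing a neighbourhood's arm from the person who screens or tests. Nor does it describe identifying or screening residents before allocation.

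**The concern.** Randomising neighbourhoods makes the neighbourhoods comparable in expectation. It does not by itself make the people enrolled from them comparable if enrolment happens after the arm is known to those who decide on entry. Here an address reveals the arm to anyone who knows the allocation.

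The entry criteria also touch the primary outcomes. Self-reported cognitive problems exclude, and cognitive functioning is primary. Walking ability and mobility-limiting illness bear on physical activity, which the Outcomes section also names as primary. If a screener who knows the arm probes these points more strictly in one arm, the groups differ at the start for a reason unrelated to treatment.

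The baseline cognitive test comes after allocation too. A tester who knows the arm could affect the very measurement that would later be used to correct an imbalance.

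**Working it through.** **1. Order of events.** Taking Recruitment and Procedure together, the sequence is: neighbourhoods selected, arm assigned, names drawn, letter sent, consent returned, phone check, accelerometer week, cognitive test, questionnaire, first advice (experimental arm only). Every step that decides who enters, and every baseline measurement, follows assignment of the arm.

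**2. Is non-blinding forced at these steps?** Up to and including the baseline questionnaire, the described handling is the same in both arms. The arms separate when the tailored advice is generated, and a computer program does that. The nature of the intervention therefore gives no reason why the phone screener or baseline tester must know the arm.

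**3. The plan's own sample size, as the reference for scale.** Inputs from the sample size section: effect size .30, power .80, ICC .01, 190 per group, 30% dropout, 270 per group. Two-sided 5% alpha is assumed, as it is not stated.
- Without clustering: 2 × (1.96 + 0.84)² / 0.30² ≈ 175 per group.
- Implied design effect: 190 / 175 = 1.086.
- Dropout: 190 / 0.70 = 271.4, so 272 against the stated 270.

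The figures are consistent. The concern does not change the sample size.

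**4. What an imbalance would mean (assumed, not from the document).** Let b be a difference between arms in SD units caused by screening.
- b = 0.05: 0.05 / 0.30 = 17% of the planned effect.
- b = 0.10: 0.10 / 0.30 = 33% of the planned effect.

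For an unadjusted comparison with about 175 effective participants per group and no true effect, SE = √(2/175) = 0.107. The two-sided rejection rate is Φ(−1.96 + b/SE) + Φ(−1.96 − b/SE):

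| b (SD) | rejection rate |
|---|---|
| 0 | 5.0% |
| 0.05 | 7.5% |
| 0.10 | 15.5% |

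These rates assume that all of b carries through to follow-up. Baseline adjustment would remove part of it.

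**5. Would the planned baseline tests reveal it?** With 270 per arm and no clustering, the SE of a baseline difference is √(2/270) = 0.086 SD. A true difference of 0.10 SD gives 0.10 / 0.086 = 1.16, well short of 1.96. If each of the two groups in the seven municipalities is taken as one cluster (14 clusters, an assumption), cluster size is 540 / 14 = 38.6, the design effect is 1 + 37.6 × 0.01 = 1.376, and the SE is 0.086 × √1.376 = 0.101. Either way, a non-significant baseline test is weak reassurance. The limiting factor is the small size of the imbalance, not mainly the number of clusters.

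**The case against.** **Self-selection is largely closed.** Participants are unaware of two groups and are invited by a municipal letter with no arm-specific wording described. Residents have no stated basis for volunteering differently by arm. This stands, and it confines the concern to staff.

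**The screener's knowledge is inferred.** The article says that "it is not possible to blind the researchers" and gives the phone check to a research assistant. It does not say that this assistant knows the arm. Custody of the allocation list may be set out in a fuller protocol, and the procedure figure is not available here. This also stands. But the published statement is unqualified, and nothing in the article limits it to staff who deliver the intervention.

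**Discretion is limited.** Age, wheelchair use and walking 100 m are mostly factual, cognitive problems are self-reported, and much of the testing runs on tablet software. This reduces the room for bias. It does not remove it: whether a condition may affect mobility, or how far a cognitive complaint is pursued by phone, leaves some judgement.

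**Stronger readings that the document does not support.**
- A reader might infer that the arms will differ. The article shows only that they can.
- A reader might compare 540 enrolled with the 3,500 to 28,000 residents drawn (7 × 500 to 7 × 4000), about 2% to 15%, and infer ample room for staff selection. That ratio mostly reflects non-response and ineligibility. Staff act only on those who returned consent, and the number they screen out is not known.
- A reader might take a fixed share of the target effect as the expected bias. No imbalance is documented, and the Statistical analyses section does not commit to an unadjusted contrast.

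**Conclusion.** The point holds as a risk in the stated procedure. Allocation precedes invitation, screening and baseline testing; no concealment from screeners or testers is described; and the non-blinding statement is broader than the design requires. The remaining routes are differential screening by staff and unmasked baseline testing.

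The size cannot be derived from the document. The 17% to 33% of the planned effect rests wholly on an assumed imbalance of 0.05 to 0.10 SD and applies before baseline adjustment. The point also assumes that screeners and testers are among those not blinded, which is inferred. The change is worth making because it removes an avoidable route to bias in the primary comparison at little cost.

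**What to change.** - Keep the neighbourhood allocation list from phone screeners and baseline testers for the whole recruitment period in each municipality. Releasing the arm to them participant by participant would not work, because one participant's allocation reveals it for the whole neighbourhood.
- Let the tailoring software, or an existing team member who does no screening or testing, hold the list and trigger the advice after each baseline questionnaire. The first advice is then not delayed.
- Restrict the non-blinding statement to staff who deliver the intervention.
- Adjust each cognitive outcome for its own baseline value, rather than leaving this to covariate selection by bivariate correlation.
- Report the numbers invited, consenting and screened out, with reasons, by arm.

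**Cost.** A small burden of separating roles; no added visits. If recruitment is already under way, apply the masking to the remaining screening and testing, and state who knew the arm and when. Baseline adjustment will not correct differences in unmeasured prognosis, or a baseline score influenced by an unmasked tester, so it supplements the masking and does not replace it.

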**Fig. 1 Fig1:**
[figure not shown]
Schematic overview of the randomized controlled trial procedure and the intervention

Before the CF test, participants in both groups receive an accelerometer device by mail with an explanation on how and when to wear it. They are asked to wear it for 7 consecutive days on their right hip. The day after the last wearing day they are visited at home by a researcher (assistant) or student who brings the accelerometer back to the research institute.

The CF tests are assessed by a trained researcher or student on an iPad Air 2 at the participants’ home with Inquisit 5 software [51]. To become familiar with the iPad, participants are asked to draw a house and a tree in the Notes application. The CF tests start with the first part of the 15 Words Learning Task, a Dutch adaptation of the Rey’s Verbal Learning Task, followed by the Trail Making Test part A and B, the Stop Signal Task, and the Letter Digit Substitution Task. The test ends with the second part of the 15 Words Learning Task. The total test takes around 45 min to complete. Any occurring disturbances or difficulties in completing the test are administered. For more information on the CF tests see the outcome measures section.

After the CF test participants choose to complete the baseline questionnaire online on www.actief-plus.nl or on paper (with a prepaid return envelope). Thereafter, the 4 month lasting intervention commences for the experimental group. After 6 months and 12 months participants are contacted again to make an appointment for the second and third measurement. They wear the accelerometer device again, are visited at home to take the cognitive tests and complete a questionnaire. Procedures for the second and third measurement are similar to the first measurement. After the final assessment participants in the control group receive access to the Active Plus intervention.

#### Experimental condition

The computer tailored Active Plus intervention stimulates PA among people aged 65 or over with a chronic illness and is proven to be effective in increasing PA behavior [37, 42–45]. The intervention is systematically developed using the Intervention Mapping Protocol, and based on various theoretical models such as the Theory of Planned Behavior [52], Precaution Adoption Process Model [53], the Integrated Model for Change (I-Change Model) [54], and a self-regulation model [55]. The intervention intents to take up and sustain PA behavior by influencing (pre−/post-) motivational constructs. The pre-motivational constructs addressed are awareness and knowledge among others. Constructs such as intention, social influence, intrinsic motivation, attitude and self-efficacy are addressed in the motivational stage. Post-motivational constructs include action planning, coping planning, strategic planning, commitment, and self-regulation skills. Especially for the targeted population of ECI tailored information is added on several chronic illnesses, the risks of sedentary behavior, and the benefits of PA for CF.

Participants in the experimental group receive advice on three occasions (see Fig. 1), tailored to the answers they give in questionnaires. The first personal advice is delivered right after the baseline assessment. Participants receive the second advice 2 months after the baseline questionnaire. And within 4 months after the baseline questionnaire feedback on progress in PA behavior is given, based on the second assessment (only used to generate a third advice). All participants in the experimental condition receive a copy of their personal advises by email (if they have registered an email address) and by mail as well. Participants receive an invitation for the follow-up assessment by mail, together with the follow-up questionnaire and a prepaid return envelope, and by email, including a link to the questionnaire.

The intervention gives tailored information on PA and its determinants especially for older adults with chronic illness(es), such as the importance of PA to maintain adequate cognitive functioning. The exact content of the advices depends on the participants’ personal characteristics (e.g. age, gender, and presence of a chronic condition) and psychosocial characteristics (e.g. the (pre−/post-) motivational constructs as described above), their current PA behavior, and to what extent they are willing to alter their behavior. Each participant in the experimental group receives all the tailored information, although the participants current PA behavior and stage of change controls in which advice the information is given. The intervention is integrated into a website where additional information on local PA possibilities (e.g. walking or cycling routes in their own neighborhood or sport clubs) can be found, as well as a user forum, and examples of PA exercises.

#### Waiting list control condition

Participants allocated to the waiting list control condition do not have access to the personalized PA advises, the additional information, user forum or examples of PA exercises until the end of the 12 month study period. As such, they have no access to any of the intervention features, and are encouraged to continue with their usual activities. After the study period they receive their personalized PA advises.

### Outcomes

As it is the main goal of the current project to test if the Active Plus program is able to increase CF or to slow down its decline by means of sufficient PA, the primary outcomes are CF and PA. Secondary outcome measures are self-reliance, health related quality of life, and loneliness. Outcomes are assessed at baseline, and after six and 12 months.

#### CF outcomes

The Verbal Learning Test (VLT) [56] is a frequently used measure of verbal memory. Several studies found PA interventions effective in improving memory [19]. As memory complaints are often the first cognitive complaints people suffer from this aspect of cognitive functioning is also included in the current study. In this test, 15 words are presented one by one on an iPad screen in fixed order, with a presentation time of 1 s and an interstimulus interval of 1 s. Afterwards participants are asked to verbally recall the words they have remembered. The first trial is followed by four more trials in which the words are presented in identical order. After a delay of 15–25 min in which the remaining CF tests are assessed, and unexpectedly for the participants, the instruction is given to recall the 15 words learned once more. Finally, a recognition trial is administered. Greater test scores indicate better verbal memory.

The Letter-Digit Substitution Test (LDST) [57] is a modification of the procedurally identical Symbol-Digits Modalities Test [58]. This test is often used as a measure of processing speed of general information, which is found to be affected by PA [20]. In the LDST, letters are presented and the participant has to respond by clicking the corresponding digits, according to a key. After a practice round of 10 letters, the participant has 60 s to replace the randomized letters with the appropriate digit indicated by the key. Greater test scores indicate better speed of information processing.

The Trail Making Test (TMT) provides information on visual search, scanning, speed of processing, mental flexibility, and executive functions [59]. The TMT consists of two parts. TMT-A requires the participant to draw lines with their finger sequentially connecting 25 encircled numbers distributed on the iPad. Task requirements are similar for TMT-B except the participant must alternate between numbers and letters (e.g., 1, A, 2, B, 3, C, etc.). The score on each part represents the amount of time required to complete the task. Score on B-A is a measure for shifting, which is a construct of executive functioning and is found to be affected by PA [60]. The larger the score B-A is, the more difficulty the participant has with shifting.

The Stop Signal Test is a useful test for the investigation of response inhibition which is a construct of executive functioning and is affected by PA [60, 61]. The task is to press the left response key if the arrow on the iPad screen points to the left and press the right response key if the arrow points to the right unless a signal beep is played after the presentation of the arrow. In this case the response should be stopped before execution (inhibition). The test consists of two parts: The first part is a practice block of 32 trials. Afterwards, three blocks of 64 trials are taken with 10 s of rest in between blocks. The delay between presentation of arrow and signal beep, starting at 250 milliseconds (ms), is adjusted up or down by 50 ms depending on performance. The delay gets longer if the previous signal stop was successful (up to 1150 ms) and it gets smaller if the previous signal stop was not successful (down to 50 ms). Thus, the task uses a staircase design for the stop signal delay (SSD), allowing the task to adapt to the performance of the participant, narrowing in on the 50% success rate for inhibition. Outcome measure is an estimation of the stop signal reaction time in ms (SSRT), which is the time required to stop the initiated go-process. The slower the SSRT the more difficult to stop the go-process.

#### PA outcomes

Self-reported PA is measured using the validated Short Questionnaire to Assess Health Enhancing Physical Activity (SQUASH) [62], assessing activities regarding household and leisure time and sports. For each activity the frequency, the duration and the intensity is administered. The SQUASH questionnaire classifies PA into light (metabolic equivalent (MET) < 3.0), moderate (MET 3.0–5.9), and vigorous (MET > 6) [63]. The scoring manual is used to calculate these constructs and to exclude any extreme values. The SQUASH has reasonable reliability (ρ = .58) and validity (ρ = .45) opposed to an accelerometer [62].

PA is also measured using the ActiGraph GT3X-BT (ActiGraph, Pensacola, FL). Participants wear the accelerometer on an elastic belt on their right hip for 7 days. During the night participants are not obliged to wear the device. Participants are asked to remove the devices while showering or swimming. Data is downloaded and analysed using ActiLife software. Measurements are considered valid if there is at least 4 days of data with at least 10 h of wear time per day [64]. Non-wear periods are eliminated from the analyses and are identified with the Choi algorithm [65]. The Choi algorithm identifies 90 min of consecutive zero counts as non-wear time, which may be interrupted by a maximum of 2 min of non-zero counts. To distinguish between light, moderate and vigorous PA the software uses data from 3 axes based on 60 s epochs. Freedson-VM cut-off points, developed by Sasaki [66], and the cut-off points developed by Aguilar-Fariaz [67] are used as algorithms to determine the average hourly and daily time spent per metabolic rate.

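### The accelerometer rules do not tie the 10-h valid day or the hourly average to waking time, although night wear is optional and Choi removes sleep only in part

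*Protocol article*

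**What the plan says.** The PA outcomes section of the protocol article sets out the accelerometer processing almost from end to end.

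- Wear: "Participants wear the accelerometer on an elastic belt on their right hip for 7 days". On nights: "During the night participants are not obliged to wear the device". Night wear is thus neither required nor ruled out.
- Validity: "Measurements are considered valid if there is at least 4 days of data with at least 10 h of wear time per day". The rule refers to wear time, not waking wear time.
- Exclusion: "Non-wear periods are eliminated from the analyses and are identified with the Choi algorithm". The algorithm "identifies 90 min of consecutive zero counts as non-wear time, which may be interrupted by a maximum of 2 min of non-zero counts". No other exclusion is stated: no sleep detection, no time-in-bed log, no clock window.
- Summary: the cut-points "are used as algorithms to determine the average hourly and daily time spent per metabolic rate".

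The Outcomes section states that "the primary outcomes are CF and PA". The Background makes the link between the characteristics of activity and cognition another primary objective, and the Statistical analyses section plans a moderation analysis on type, duration, frequency and intensity.

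**The concern.** Taken together, these rules let a personal habit enter the measurement. Two people with identical waking behaviour can have different wear time if one keeps the belt on in bed and the other takes it off. The same can happen to one person between baseline, 6 and 12 months.

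Whatever part of a worn night survives the Choi rule has three consequences:

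- it counts towards the 10 h, so a day can qualify with fewer than 10 waking hours observed;
- it enlarges the denominator of the hourly averages without adding activity;
- it is scored in the lowest intensity class.

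At stake is the precision of the accelerometer outcome, of its change over time, and of the relation between activity and cognition in the moderation analysis.

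**Working it through.** The plan gives no figure to reproduce here, so this is an illustration.

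**Inputs from the document:** valid day of at least 10 h of wear; Choi non-wear of at least 90 min of zeros with up to 2 min of non-zero counts; hourly and daily averages.

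**Assumed inputs, because the document gives none:** 30 min of moderate-to-vigorous activity a day; W = 15 waking hours of wear; N = 8 h of night wear; f = share of the worn night that Choi removes, varied from 0 to 1.

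**Formulas**

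- Hourly value = 30 / (W + N × (1 − f))
- Waking hours needed for a valid day = 10 − N × (1 − f)
- Night minutes added to the lowest class = 60 × N × (1 − f)

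Without night wear the hourly value is 30/15 = 2.00 min/h, and a valid day needs 10 waking hours. With night wear:

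| Share removed by Choi (f) | Wear hours | Hourly value (min/h) | Change | Waking hours for a valid day | Minutes added to lowest class |
|---|---|---|---|---|---|
| 1 | 15 | 30/15 = 2.00 | 0% | 10 − 0 = 10 | 0 |
| 0.75 | 15 + 2 = 17 | 30/17 = 1.76 | −12% | 10 − 2 = 8 | 120 |
| 0.5 | 15 + 4 = 19 | 30/19 = 1.58 | −21% | 10 − 4 = 6 | 240 |
| 0 | 15 + 8 = 23 | 30/23 = 1.30 | −35% | 10 − 8 = 2 | 480 |

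The percentage change does not depend on the 30 min, since the ratio is W / (W + N × (1 − f)).

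**Sensitivity to W and N** (W from 12 to 16 h, N of 7 or 8 h)

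- f = 0.5: the fall runs from 1 − 16/19.5 = 18% to 1 − 12/16 = 25%.
- f = 0: the fall runs from 1 − 16/23 = 30% to 1 − 12/20 = 40%.

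**Daily minutes.** With all 15 waking hours recorded, daily moderate-to-vigorous time is 30 min in every row. It can be understated only on a day that reaches 10 h with the help of night wear while waking hours are missing. For example, 6 waking hours is 6/15 = 40% of the assumed waking day.

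**Under a waking-time rule** the case equals f = 1 for everyone: 2.00 min/h whether or not the device is worn in bed, and 10 waking hours for a valid day.

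**The case against.** The strongest reply is that the article never says night wear counts. It is silent on sleep, and a condensed article may leave a sleep filter to a fuller document. It also says, under Procedure, that the device comes with an explanation of its use that covers timing, and that later measurements follow similar procedures. That explanation is not shown and may already deal with bedtime. Choi, as described, deletes still stretches of 90 min or more, which could be much of a quiet night. The section treats night as the exempt period, so wearing the belt all night and hardly at all by day would be unusual behaviour. Activity is also measured by questionnaire, and the sample size rests on cognition.

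Most of this limits the size of the problem and does not remove it. The section gives the valid-day rule, the non-wear algorithm with its parameters, the epoch, the cut-points and the summaries. Applied as written, that chain keeps any worn night time that Choi does not flag.

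Three stronger readings are tempting but not supported:

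- A reader might infer that a valid day routinely holds only about 2 waking hours. That needs a full 8-h night with nothing removed.
- A reader might infer that all activity values shift with night wear. Daily moderate and vigorous minutes do not when waking data are complete.
- A reader might infer bias between the arms. Nothing suggests that night wear differs by arm, and participants do not know that two groups are compared.

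**Conclusion.** The point holds as a gap between the wear instruction and the processing rules. The 10-h rule and the hourly average are not anchored to waking time, and the one stated exclusion removes sleep only in part. Under the stated assumptions the hourly value is diluted by 0% to 35%, with 21% if half the night is removed. The waking data needed for a valid day fall from 10 h to 6 h at half removal and to 2 h at the extreme. The true position in that range depends on how many people wear the device at night and how much of the night Choi flags; the document gives neither.

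The expected effect is added noise and inconsistency between people and visits, mainly in the hourly and lowest-intensity values. It is not a demonstrated bias in the comparison of arms. It is still worth correcting, because the accelerometer measures part of a primary outcome and feeds the moderation analysis, and the remedy is cheap.

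**What to change.** State in the PA outcomes section that only waking time is analysed. Define it by marked sleep periods or by one pre-set clock window, identical at baseline, 6 and 12 months. Apply this restriction first, then Choi, then the 10-h, 4-day rule, and compute hourly and daily values on waking wear time only. If the explanation sent with the device already asks for removal at bedtime, say so there.

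The cost is a filter step in processing, which can also be applied to recordings already made. The downside is small: some activity outside the window is lost, a few recordings become invalid, and a clock window would still admit time in bed that falls inside it.
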